TIA is defined as a transient episode (duration of symptoms < 24 h) of neurological dysfunctions caused by focal brain, spinal cord, or retinal ischemia without showing acute infarction on non-contrasted CT (NCCT).Ischemic stroke is a persistent episode of neurological dysfunctions caused by focal brain, spinal cord, or retinal ischemia, which shows acute hypodense infarction area on NCCT images and T2-weighted MRI.Angina is defined as a transient chest pain or pressure (duration of symptoms < 30 min) caused by insufficient blood flow to the myocardium without significant ST/T changes in ECG and rise of cardiac biomarkers.Myocardial infarction is defined as myocardial necrosis in clinical settings consistent with myocardial ischemia. These conditions can be satisfied by a rise of cardiac biomarkers [preferably cardiac troponin (cTn)] plus at least one of the following: (1) symptoms of cardiovascular ischemia; (2) ECG changes indicative of new ischemia (significant ST/T changes or left bundle branch block); (3) development of pathologic Q waves; (4) imaging evidence of new loss of myocardium or new regional wall motion abnormalities; (5) angiography or autopsy evidence of intracoronary thrombus.

Secondary outcomes are: 1. UIA rupture events during 24-month follow-up; 2. UIA growth events during 24-month follow-up; 3. Change in average Wall Enhancement Index (WEI) at baseline and 24th month. WEI is defined as follows:

Two investigators (with work experience of >10 years, who are blind to the clinical and morphological information) measure the WEI value independently using Vessel-MASS software (Leiden University Medical Center). Three slices with significant enhancement observed by post-contrast VW-MRI at baseline and 24 months will be selected. After tracing the lumen and outer boundaries of the aneurysm wall, the contours of the inner lumen and outer wall of aneurysms will be automatically segmented using the software. If the tracking is not satisfactory, the investigators will manually adjust the contour of the inner cavity and the outer wall. Subsequently, the mean signal intensity (SI) will be calculated automatically using the software. The average and maximum value of the mean SI of the corresponding three slices will be used for further analyses.

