#### Step 3: Outcome evaluation

All patients will be required to complete head CTA at 6 months (± 1 month), 12 (± 1 month) months, and 24 (± 1 month) months during follow-up. VW-MRI examinations are required to be completed at 24 (± 1 month) months after appropriate blood pressure lowering therapy.

Self-record blood pressure and occurrence of any aneurysm-related symptoms or safety endpoints (ischemic cerebral or cardiac events) will be recorded every month via outpatient or phone review during follow-up.

Patients will use self-monitoring methods to monitor blood pressure during the follow-up. All patients are required to measure the blood pressure of the left brachial artery twice per week. Before blood pressure measurement, patients will be required to rest quietly for at least 5 min. Blood pressure will be measured using the YUYUE electronic sphygmomanometer (YE660A, China, which can record 40 data points in built-in memory). The data on blood pressure will be collected once a month (8-week blood pressure data will be collected from an electronic sphygmomanometer). The average of 8 systolic pressures will be calculated and used as the monthly pressure in statistical analysis.

For both randomized groups, protocol visit frequency will be monthly. During follow-up, outcome assessors who are blinded to patients’ treatment allocation will independently record all relevant events in detail:

UIA instability (the occurrence time, treatment and radiological data);Monthly self-monitoring blood pressure (8-week blood pressure data will be collected from an electronic sphygmomanometer. The average of 8 systolic pressures will be calculated and used as the monthly pressure);Ischemic cerebral or cardiac events (the occurrence time, treatment and radiological data).Regular follow-up head CTA [6 months (± 1 month) 12 (± 1 month) months, and 24 (± 1 month) months].

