### Quality control of the research

To avoid bias and ensure patients’ medical adherence, we follow the standards in the subsequent text:

Self-monitoring of blood pressure: According to the recommendation of China’s guideline for hypertension (2018) (16), we will use the home blood pressure monitoring method to monitor patients’ blood pressure monthly. All patients will receive training for blood pressure measurements from professional cardiologists at enrollment and every 3 months. We will evaluate pre-enrollment medication adherence and include only patients with good adherence. We will require all patients to measure the blood pressure of the left brachial artery twice at least 1 min apart in the morning before breakfast and taking antihypertensive medications, and after urination and defecation. Before blood pressure measurement, all patients will be required to rest for at least 5 min. Blood pressure is measured using the YUYUE electronic sphygmomanometer (YE660A, China). Researchers will collect blood pressure data once a month.Protocol-noncompliance: If the patient’s SBP does not reach the assigned target during follow-up, the cardiologists will evaluate the patient according to the predefined antihypertensive treatment algorithm (Figures 2, 3).Unable to complete the required CTA examinations: We will contact each patient one month before the CTA examination by telephone to ensure completion. If patients are unable to complete CTA examinations in the required time interval, they will not be included in the final analysis.

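### The wall-enhancement outcome measures slices chosen because they enhance at 24 months, so the month-24 measurement is selected on the outcome and non-enhancing walls have no qualifying slice

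*Protocol article*

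**What the plan says.** In the protocol article, section Outcomes and relative definitions, the third secondary outcome is "Change in average Wall Enhancement Index (WEI) at baseline and 24th month". The slices to be read are fixed by this sentence: "Three slices with significant enhancement observed by post-contrast VW-MRI at baseline and 24 months will be selected". The summary is then fixed: "The average and maximum value of the mean SI of the corresponding three slices will be used for further analyses". Two readers measure independently, "who are blind to the clinical and morphological information".

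Three other places bear on the point.

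- The inclusion criteria admit regular saccular aneurysms below 7 mm and set no condition on wall enhancement.
- Vessel-wall MRI is part of screening (Step 1) and is repeated at the end without any enhancement condition: "VW-MRI examinations are required to be completed at 24 (± 1 month) months after appropriate blood pressure lowering therapy".
- The only exclusion from analysis that is tied to a specific imaging examination concerns CTA (Quality control of the research): "If patients are unable to complete CTA examinations in the required time interval, they will not be included in the final analysis".

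**The concern.** The slices are chosen by the property that is then measured, and at month 24 that property has already been exposed to the randomised treatment. If the enhanced arm reduces enhancement, the walls that responded most are the least likely to offer three significantly enhancing slices. The comparison of WEI change would then rest on whatever still enhances, and that remainder could differ between arms because of treatment.

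Aneurysms without enhancement can be enrolled and will be scanned at both visits, so the situation can arise in this population. At stake is the interpretation of one of three secondary outcomes, the only continuous one. The primary efficacy and safety outcomes do not use WEI.

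**Working it through.** **1. Can WEI be computed for a non-enhancing wall?** Write R for the wall-to-white-matter signal ratio. The article's formula is WEI = (R_post - R_pre)/R_pre = R_post/R_pre - 1. With no enhancement R_post = R_pre, and WEI = 0. The formula works for such walls, so the restriction to enhancing slices is not needed.

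**2. Two readings of the selection sentence.** It can mean (a) that enhancement is required at both visits, or (b) that three enhancing slices are picked separately at each visit. The article's reference to the corresponding three slices does not decide between them: it points back to slices already selected on enhancement and gives no anatomical match.

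**3. Inputs.** The article gives no WEI mean, SD, correlation, threshold or expected effect, so there is no figure of its own to reproduce. All values below are assumptions for illustration.

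**4. Reading (a), enhancement required at both visits.** Assumed: baseline and 24-month WEI bivariate normal, SD 0.5, correlation 0.6, same mean at both visits in the standard arm (SBPL), true arm difference in change -0.25. The effect is either the same in everyone or concentrated in 30% of patients (0.25/0.30 = 0.83 each). An aneurysm counts only if it is above the threshold at both visits.

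Analytic check of one cell (mean 0.5, threshold 0.5, standard arm): P(both above) = 1/4 + arcsin(0.6)/(2π) = 0.25 + 0.1024 = 0.3524. P(baseline above) = 0.5. Share of baseline-enhancing aneurysms lost = 1 - 0.3524/0.5 = 29.5%. The simulation gives the same.

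| Mean WEI | Threshold | Lost, SBPL | Lost, EBPL (uniform effect) | Observed difference, uniform effect | Observed difference, effect in 30% |
|---|---|---|---|---|---|
| 0.5 | 0.25 | 19% | 37% | -0.17 | -0.04 |
| 0.5 | 0.50 | 30% | 51% | -0.15 | -0.02 |
| 0.5 | 0.75 | 42% | 65% | -0.13 | -0.01 |
| 1.0 | 0.25 | 5% | 13% | -0.22 | -0.11 |
| 1.0 | 0.50 | 10% | 24% | -0.20 | -0.07 |
| 1.0 | 0.75 | 19% | 37% | -0.17 | -0.04 |

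Every cell is closer to zero than the true -0.25.

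**5. Selection on baseline enhancement only.** In the same model, keeping aneurysms above the threshold at baseline and measuring all of them at 24 months gives -0.25 in every setting. The baseline half of the condition narrows the population but does not bias the comparison.

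**6. Reading (b), three slices chosen afresh at each visit, nobody lost.** Assumed: eight slices per aneurysm, mean WEI 0.6, between-slice SD 0.3, per-visit slice noise SD 0.15, whole-wall arm difference -0.20, and the three highest slices read at each visit.

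| Pattern of effect | Whole wall | Same three baseline-chosen slices | Three slices chosen anew |
|---|---|---|---|
| Uniform (-0.20 in every slice) | -0.20 | -0.20 | -0.20 |
| Focal (-0.40 in a random half of slices) | -0.20 | -0.20 | -0.15 |
| Proportional (one third lower) | -0.20 | -0.28 | -0.30 |

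Under reading (b) the result is unbiased, attenuated by about 26% (unrounded -0.147 against -0.200), or larger than the whole-wall effect, depending on a pattern nobody knows in advance.

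**The case against.** A reader might infer that aneurysms whose enhancement resolves are removed from the analysis, and that the treatment effect is therefore certainly biased toward zero. The article does not support that. It states no such exclusion: the closing MRI is required of everyone, the one examination-specific imaging exclusion concerns CTA, and the WEI formula gives a value near 0 for a wall that no longer enhances. The sentence can also mean simply that three slices are read at each visit. Under that reading the direction is open, as the second table shows. Attenuation follows only if enhancement is required at both visits.

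Nor does regression to the mean support the stronger claim. Where it arises from choosing bright slices at baseline, it acts on both randomised arms alike.

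It can also be said that the handling of walls with too few enhancing slices belongs in an imaging manual, and that a journal article is condensed. That would be a fair answer to a missing detail. Here, however, the article states a selection criterion, and the criterion itself depends on month-24 enhancement. Blinding the readers does not remove this: a blinded reader who follows the rule still selects on what the 24-month image shows.

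From the other side, these limits stand: the loss of resolved aneurysms is conditional, the direction is conditional, all sizes rest on assumed inputs, and the reach is one secondary outcome.

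**Conclusion.** The point holds in a conditional form. The stated rule makes the month-24 WEI measurement depend on the post-randomisation outcome and leaves walls without enhancing slices at 24 months with no qualifying measurement.

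- With enhancement required at both visits, the between-arm difference is attenuated. Under the assumptions shown, a true -0.25 loses 14% to 48% with a uniform effect (unrounded -0.216 to -0.130) and 55% to 95% with an effect confined to 30% of patients (-0.113 to -0.013).
- With slices chosen anew at each visit, different wall regions may be compared, and the estimate may be right, too small or larger than the whole-wall effect.

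These figures show mechanism and direction; they are not a forecast for this trial. The correction is worth making because it is cheap and removes the dependence under either reading.

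**What to change.** Replace the slice-selection sentence with wording such as: *Three slice positions are chosen on the baseline scan by anatomical location (for example neck, mid-body and dome), regardless of enhancement. The same positions are matched and measured at 24 months whether or not they enhance. WEI is computed for every aneurysm with both scans, including walls without visible enhancement.* Compare the arms in all randomised patients with both scans, with the average over the three slices as the single measure for this secondary outcome.

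The scans, the two readers and the software stay the same; only the reading instruction and the outcome wording change. The price is some additional contouring time and more measurement noise on walls that do not enhance.

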### Consent

The patients, or their legal representatives, are approached by the principal investigator or sub-investigator of the clinical team to ascertain their interest in participating in the ChATIA trial. When patients or their legal representatives freely and voluntarily agree to participate in this study, their signature or name/seal and the date of consent shall be obtained based on a consent form approved by the participating hospitals.

### Procedure and data collection

Data collection includes demographic information, clinical information, and radiological information. The details are shown in Table 1.

**Table 1 tab1:** Study procedures.

ChATIA-1 trial	Study procedures				
	Screening	Follow-up			
	Outpatient visit	During 24-month follow-up	6 ± 1 months	12 ± 1 months	24 ± 1 months
Randomization	○				
Clinical information	○				
Radiological examinations for UIA	○		○	○	○
Monthly Blood pressure monitor		○			
Aneurysmal symptom monitor		○			
Ischemic event monitor		○			

UIA, unruptured intracranial aneurysm.

The procedure includes patient screening and enrollment (Step 1), randomization and intervention (Step 2), and outcome evaluation (Step 3), as shown in Figure 1.

**Figure 1 fig1:**
[figure not shown]
The flow chart of study procedure. UIA, unruptured intracranial aneurysm; SBPL, standard blood pressure lowering; EBPL, enhanced blood pressure lowering.

#### Step 1: Screening and enrollment

The patients, or their legal representatives, are approached by the principal investigator or sub-investigator of the clinical team to ascertain their interest in participating in the ChATIA trial. Potential participants with UIAs will primarily be identified and recruited from outpatient clinics, where eligible patients are regularly followed for aneurysm management and blood pressure control. When patients or their legal representatives freely and voluntarily agree to participate in this study, their signature or name/seal and the date of consent shall be obtained based on a consent form approved by the participating hospitals.

Patients will receive a primary screening after obtaining consent. The evaluation includes radiological examination for UIA [CT angiography (CTA) and vessel wall (VW)-MRI], blood pressure in the past month, exclusionary conditions and medication adherence.

#### Step 2: Randomization and intervention

Enrolled UIA patients will be randomized at a ratio of 1:1 to the EBPL group and SBPL group after obtaining informed consent. Dynamic randomization using the minimization method is used as the randomization of subjects to the EBPL or SBPL group. Randomization and enrollment of subjects are made using the online randomization system. Randomization factors are as follows: age at the time of obtaining the informed consent (≥ 60 years or < 60 years), sex (female or male), aneurysm location [Anterior Communicating Artery (Acom)/Anterior Cerebral Artery (ACA), Internal Carotid Artery (ICA), Middle Cerebral Artery (MCA) and Posterior circulation (PC)]. Patients in the EBPL group are required to keep systolic blood pressure at <120 mmHg and those in the SBPL group at 120-140 mmHg.

This study aims to compare the effects of different blood pressure targets rather than specific medications. Therefore, the blood pressure treatment protocol is flexible in terms of the choice and doses of antihypertensive medications, but there should be preferences based on cardiovascular outcome trials results and current guidelines [such as thiazide diuretic, Calcium Channel Blockers (CCBs), Angiotensin-Converting Enzyme Inhibitors (ACEIs), and Angiotensin II Receptor Blockers (ARBs)]. If adopting another dose frequencies is not required (e.g., twice a day), the preference will be choosing long-acting antihypertensive agents, i.e., once per day.

The cardiologists may select among the available study antihypertensive medications for initiation of therapy. Other drugs not supplied by the trial may also be used as the cardiologists determines appropriate. However, all antihypertensive regimens should include one or more drug classes with strong cardiovascular outcome data from large randomized controlled hypertension trials. If three drugs are needed, a thiazide-type diuretic, a RAS blocker (ACEI or ARB, but usually not both), and CCB make a very effective and usually well-tolerated regimen. The decision is left to the investigator as long as the BP goals are achieved.

Once the SBP goal has been achieved in any participant, the antihypertensive regimen should be intensified if diastolic blood pressure (DBP) remains ≥100 mmHg at a single visit or ≥90 mmHg at two successive visits to achieve DBP < 90 mm Hg. The visit intervals and decisions for titration (other than the BP levels) will be similar to those used for the SBP goal. Since beta-blockers reduce DBP more than systolic BP relative to other antihypertensive medications, a beta-blocker could be considered for such participants (Figures 2, 3).

**Figure 2 fig2:**
[figure not shown]
Treatment algorithm for EBPL group (SBP < 120 mmHg). 1. May use loop diuretic for patients with advanced CKD. 2. Consider consulting a cardiologist before adding a fifth antihypertensive medication, 3. Or until clinical decision made that therapy should not be increased further. 4. Unless side effects warrant change in therapy.

**Figure 3 fig3:**
[figure not shown]
Treatment algorithm for SBPL group (SBP at 120–140 mmHg). 1. Consider consulting a cardiologist before adding a fifth antihypertensive medication, 2. Or until clinical decision made that therapy should not be increased further. 3. Unless side effects warrant change in therapy.

#### Step 3: Outcome evaluation

All patients will be required to complete head CTA at 6 months (± 1 month), 12 (± 1 month) months, and 24 (± 1 month) months during follow-up. VW-MRI examinations are required to be completed at 24 (± 1 month) months after appropriate blood pressure lowering therapy.

Self-record blood pressure and occurrence of any aneurysm-related symptoms or safety endpoints (ischemic cerebral or cardiac events) will be recorded every month via outpatient or phone review during follow-up.

Patients will use self-monitoring methods to monitor blood pressure during the follow-up. All patients are required to measure the blood pressure of the left brachial artery twice per week. Before blood pressure measurement, patients will be required to rest quietly for at least 5 min. Blood pressure will be measured using the YUYUE electronic sphygmomanometer (YE660A, China, which can record 40 data points in built-in memory). The data on blood pressure will be collected once a month (8-week blood pressure data will be collected from an electronic sphygmomanometer). The average of 8 systolic pressures will be calculated and used as the monthly pressure in statistical analysis.

For both randomized groups, protocol visit frequency will be monthly. During follow-up, outcome assessors who are blinded to patients’ treatment allocation will independently record all relevant events in detail:

UIA instability (the occurrence time, treatment and radiological data);Monthly self-monitoring blood pressure (8-week blood pressure data will be collected from an electronic sphygmomanometer. The average of 8 systolic pressures will be calculated and used as the monthly pressure);Ischemic cerebral or cardiac events (the occurrence time, treatment and radiological data).Regular follow-up head CTA [6 months (± 1 month) 12 (± 1 month) months, and 24 (± 1 month) months].

Milepost visit: Milepost visits are used to assist in reaching goal SBP. In this trial, milepost visits will be every 6 months throughout follow-up in both the EBPL group and SBPL group (6th month, 12th month, and 18th month). During each milepost visit, patients will be asked to visit the nearest participating hospital, where cardiologists will measure their blood pressure. This measured blood pressure will be recorded as the milepost visit blood pressure. If the SBP exceeds the target value at milepost visit, then an antihypertensive drug from a class different from what is being taken should be added. Once participant has been prescribed five drugs at maximally tolerated doses, if the SBP remains above goal at subsequent milepost visits, it will be permitted to substitute a different class into the regimen instead of adding another drug or increasing the dose of a drug. However, additional (more than 5) drugs may be needed to achieve goal SBP in some participants. Medication adherence will be assessed routinely in the current trial and should be evaluated especially carefully for participants not at goal on 4 or more medications. Strategies to enhance adherence should be applied.

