### Outcomes and relative definitions

The primary efficacy outcome is UIA instability, including aneurysm growth, rupture or aneurysm-related symptoms during 24-month follow-up. The definitions of UIA instability are listed as follows:

Aneurysm growth is defined as one or more of the following: (1) growth of more than 1 mm in at least one direction, (2) growth of more than 0.5 mm in at least two directions, (3) growth of more than 20% of baseline aneurysm size in any direction, or (4) new appearance of irregularity on the UIA.Aneurysm rupture is diagnosed when patients have the symptoms of non-traumatic subarachnoid hemorrhage (e.g., severe headache and sudden coma) attributable to the target UIA, imaging evidence of hemorrhage on CT or MRI, and/or bloody cerebrospinal fluid from lumbar puncture.Occurrence of aneurysm-related symptoms is diagnosed as sentinel headache (a sudden and severe headache attributable to the UIA within 2 weeks of onset, and without prior history of significant headache within the previous 5 years), oculomotor nerve palsy (a sudden headache with one or several symptoms of pupillary light reflex disappearing, ptosis, or extraocular myoparalysis, ipsilateral to a UIA in the vicinity of the affected oculomotor nerve and without systemic cause such as diabetes), other cranial neuropathy (such as visual field defect secondary to UIA compression of the optic apparatus without alternative cause), or seizure related to UIA inflammation (defined as EEG or clinically determined seizure activity generated from inflammatory changes in the brain parenchyma surrounding the UIA on imaging, and without prior history of seizure or other cause of seizure).

Two investigators who are unaware of the patient’s information assess the occurrence of UIA instability and ischemic brain or cardiac events at 6 months (± 1 month), 12 (± 1 month) months, and 24 (± 1 month) months through monthly follow-up and imaging examinations of UIA.

The primary safety outcome is any ischemic cerebral or cardiac events during 24-month follow-up. This includes one or more of the following: new or more frequent transient ischemic attacks, new clinical or radiological ischemic stroke, angina, new myocardial infarction, or reperfusion therapy for myocardial infarction. Ischemic brain or cardiac events are defined as follows:

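### The assessors called blinded are also told to record each patient's monthly SBP, the variable that defines the arms, so the stated blinding cannot be reliably maintained

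*Protocol article*

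**What the plan says.** Under Step 3: Outcome evaluation, the protocol article states that "outcome assessors who are blinded to" patients' "treatment allocation will independently record all relevant events in detail". The list of what they record then includes:

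- "UIA instability (the occurrence time, treatment and radiological data");
- "Monthly self-monitoring blood pressure (8-week blood pressure data will be collected from an electronic sphygmomanometer"), averaged to give the monthly pressure;
- "Ischemic cerebral or cardiac events (the occurrence time, treatment and radiological data");
- the scheduled head CTAs.

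Under Step 2: Randomization and intervention, the arms are set by SBP alone: "Patients in the EBPL group are required to keep systolic blood pressure at <120 mmHg and those in the SBPL group at 120-140 mmHg". The choice of drugs is left open in both arms.

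Three other sections bear on who does what.

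- **Outcomes and relative definitions:** two investigators who do not know the patient's details "assess the occurrence of UIA instability and ischemic brain or cardiac events at 6 months", 12 and 24 months. They do so by way of the monthly contacts and the imaging.
- **Quality control of the research:** researchers gather the pressure readings each month. Which researchers is not stated.
- **Safety monitoring:** an Event Adjudication Committee makes the final determination of safety outcomes. Whether it is masked is not stated, and the primary efficacy outcome is not in its remit.

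**The concern.** The trial is open-label, so masked outcome assessment is its main safeguard against detection bias. Step 3 gives the assessors it calls masked the one measurement on which the arms are meant to differ. A person who files a patient's SBP every month and also records whether the aneurysm has become unstable can often work out the arm.

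Parts of both primary outcomes depend on judgement. On the efficacy side these are growth near the 0.5 mm, 1 mm or 20% thresholds, new irregularity of the aneurysm, and symptoms that must be attributed to it. On the safety side they are mainly TIA and angina. An assessor who expects the lower target to protect the aneurysm, or to cause ischemia (a risk the Discussion itself raises), could shift borderline calls in either outcome without intending to.

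**Working it through.** The plan states no figure on this point, so the check is a comparison of sections followed by two illustrations.

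**1. Are the two tasks kept apart anywhere?**

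- Step 3 puts both tasks on one list for one group of people.
- The outcome definitions describe two investigators without the patient's details, but have them work through the monthly contacts. Step 3 says that self-recorded pressure, aneurysm symptoms and ischemic events are all taken at those contacts. The two descriptions conflict, and the second does not repair the first.
- The quality-control section does not say that the researchers who gather pressures are different people from the assessors.
- The adjudication committee covers safety outcomes only.
- The readers of the Wall Enhancement Index are separately described as blind to clinical information. That secondary outcome is not affected.

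**2. How well does SBP identify the arm?**

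The target ranges do not overlap, so if every patient in both arms were at goal, SBP would identify the arm with certainty. Achieved pressures will overlap. Let d be the difference between arm means and s the SD of a monthly mean within an arm. The document gives neither, so both are assumed. With normal distributions, equal arms and a cut midway between the means:

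P(correct arm) = Φ(d / 2s)

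| d (mmHg) | s (mmHg) | d / 2s | P(correct) |
|---|---|---|---|
| 10 | 10 | 0.50 | 69% |
| 10 | 7 | 0.71 | 76% |
| 15 | 10 | 0.75 | 77% |
| 15 | 7 | 1.07 | 86% |

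Wider assumptions give 63% (d = 8, s = 12) to 89% (d = 15, s = 6). Guessing gives 50%. Further monthly values sharpen the guess only as far as they average out within-patient variation. If s is mostly between-patient variation they add little, and the document does not allow that split to be made.

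**3. What could this do to the efficacy result?**

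Suppose there is no true effect and the true risk is p in both arms. Let f be the fraction of primary events that are borderline growth. If 20% of those are under-called in the enhanced arm alone (an assumed rate), the counted risks are p(1 − 0.2f) and p, so

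RR = p(1 − 0.2f) / p = 1 − 0.2f

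| f | RR |
|---|---|
| 0.3 | 0.94 |
| 0.5 | 0.90 |
| 1.0 | 0.80 |

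For scale, the Sample size section assumes a 50% reduction. A spurious 10% reduction (f = 0.5) is 10/50, or one fifth, of that.

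**The case against.** The strongest reply is that recording is not assessing. Step 3 says who records. The outcome definitions say who assesses, and describe those two people as lacking the patient's details. The Step 3 list also mixes true events with routine data such as scheduled CTAs, which suggests loose condensation, and an article may leave detailed role separation to the full protocol. This has some force: it shows that the sponsor intends masking, and that the CTA measurement itself could be masked if other people read it. It does not settle the matter. The text explicitly assigns both tasks to the same people, and the two investigators are sent to the contact at which pressure is taken. The fault lies in what is stated, not in missing detail.

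Several stronger readings are tempting and go beyond the document.

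- **That outcome assessment is simply unblinded.** The article claims masking twice. What can be said is that the procedure, followed as written, undermines it.
- **That SBP gives the arm away outright for a patient at goal.** An assessor who sees 118 or 128 mmHg does not know whether that patient is at goal. On the main assumptions above, 14–31% of guesses would be wrong.
- **That the bias amounts to a risk ratio of 0.80.** That requires every primary event to be borderline growth, whereas the outcome also includes rupture, symptoms and clear growth.
- **That masked assessment is the only protection.** Allocation uses an online minimization system, growth has numerical thresholds on scheduled CTA, and rupture calls for evidence of hemorrhage on imaging and/or in cerebrospinal fluid.

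**Conclusion.** The point holds as a contradiction within the article. The people said to be masked are assigned the variable that defines the arms, and no other section separates the roles, so the stated blinding cannot be reliably maintained. SBP is a strong but imperfect clue: about 69–86% correct from one monthly mean, on an assumed separation of 10–15 mmHg and SD of 7–10 mmHg. The exposure is concentrated in borderline growth and irregularity, symptom attribution, and TIA or angina. The possible efficacy bias is RR = 1 − 0.2f under an assumed 20% under-calling in one arm, so 0.90 if half the events are borderline growth. These sizes are illustrations, since the document gives no achieved separation, SD or share of borderline events. The conflict between the sections depends on none of them.

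**What to change.** 1. In Step 3, take monthly blood pressure off the outcome assessors' list. Assign its collection, and the monthly patient contact, to the clinical research coordinator, who already asks participants about adverse events at each follow-up, or to the treating cardiologist.
2. Have the two investigators named in the outcome definitions judge instability and ischemic events from de-identified CTAs and event narratives with SBP, drug list and arm removed. Delete the statement that they work through the monthly follow-up.
3. Give the Event Adjudication Committee the same masked packets for safety outcomes, and state that it is masked.
4. Reconcile the outcome definitions, Step 3, the quality-control section and the safety-monitoring section so that each names the same people for the same task.
5. If any assessments have already been made with pressures in view, have the stored CTAs re-read masked.

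The cost is modest: an existing task moves to existing staff, and preparing redacted packets is new work. Treatment rules and sample size do not change. One limit remains. Patients know their arm and report symptoms at the monthly contact, so symptom reports stay open to reporting bias however the packets are masked.
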